### Assessments only at baseline

Assessments only at baseline are measures with the purpose to characterize the participants and are only considered outcomes for cross-sectional comparisons between groups at baseline.Pulmonary function testing will be performed including spirometry, lung volumes, and diffusion capacity for carbon monoxide according to ATS/ERS guidelines [53–55]. At follow-up testing, a spirometry is performed for up-to-date pulmonary data during cycling tests.Anthropometrics: to measure height, participants will stand against a stadiometer without shoes. Body weight loss and malnutrition will be assessed using the Self-MNA® Mini Nutritional Assessment. The Self-MNA® consists of 5 questions related to food intake, weight loss, mobility, recent psychological stress or acute disease, neuropsychological features (dementia/sadness), and three anthropometric assessments (height, weight, and calf circumference), resulting in a calculated score (maximal 14 points). Based on the score, the participant is categorized as malnourished (0–7 points), at risk of malnutrition (8–11 points), and normal nutritional status (12–14 points). The Self-MNA® is the self-report version of the MNA short form that has been previously used in COPD [56], validated against the full MNA [57], and is advised to use as a nutritional screening tool by the European Society for Clinical Nutrition and Metabolism guidelines [58]. The administration of the Self-MNA® takes less than 5 min to complete.Information on smoking status and habits, pack years, exacerbations, and hospitalisations during the last 12 months, medical history, comorbidities, pharmacological treatments (any changes in medication will also be collected during the trial period), educational level, and history of risk factors for COPD (i.e., biomass exposure, occupational exposure, and host factors).Information on training status: any previous training experience, aerobic training experience, and specifically, exercise habits (type, frequency, intensity) in the last 12 months.The modified medical research council (mMRC) dyspnoea scale (0–4, arbitrary units) will be used to assess baseline dyspnoea [59]. The mMRC dyspnoea scale is used to evaluate the degree of baseline functional disability in patients with respiratory diseases [59]. The scale consists of five levels ranging from 0 to 4, each representing a different level of dyspnoea where grade 0 is the lowest degree of functional disability, and 4 the highest. The scale is easy and efficient to use and widely used in the COPD literature and is integrated with the Global Initiative for Chronic Obstructive Lung Disease (GOLD) clinical classification scheme [2]. The mMRC takes 2–3 min to complete.Physical activity (see description above).

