### Trial design

COPD-HIIT is a prospective, multi-centre, randomized, controlled, parallel-group superiority trial with the assessor and statistician blinding, featuring a 1:1 allocation ratio and two separate phases. In phase 1, we will investigate the effects and mechanisms of a 12-week intervention with supramaximal HIIT compared to MICT in people with COPD and matched healthy controls. Upon completion of the initial 12-week intervention and follow-up assessments, people with COPD, but not healthy controls, will enter phase 2 of the trial. Phase 2 comprises a 21-month maintenance exercise program. Subsequently, exercise training (supramaximal HIIT or MICT) will be performed until a 24-month follow-up. A separate control group of people with COPD, receiving usual care only, will undergo assessments at baseline and 24 months. As the usual care arm is not included in the randomization, phase 2 is a partially randomized controlled trial. See Fig. 1 and Fig. 2 for an overview of the COPD-HIIT project design.

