#### Passive control group: usual care

The passive control group will receive usual care alone and a standardized phone call (see additional file 4) every 3 months including assessment of symptoms of exacerbations. Health status (CAT) and disease-specific quality of life (CRQ) will be assessed by sending a letter with the questionnaires via the post for self-administration or by a phone call. We will match the participants in the usual care group to those randomized to HIIT or MICT by age, sex, disease severity (GOLD A/B/E), educational level, and physical activity.

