### Multicentre trial and covariates

The specific trial design is a stratified multicentre trial with individual randomization at each involved centre. Using this design results in a gain in power [126], not a loss in power typical of randomized cluster trials where observations on individuals in the same cluster tend to be correlated. Therefore, no increase in the sample size is necessary even though we collect data at two research centres. In contrast, the sample size could be reduced for a given power [126]. Furthermore, in the statistical analysis (described below), we will adjust the analysis for the predictive covariates age, sex, VO_2_peak, and centre—the latter as appropriate when stratifying the randomization. Adjusting for covariates in the statistical analysis is also associated with a gain in statistical power, or equivalently, a reduced sample size requirement [127–129]. Yet, we have taken a conservative approach and have not accounted for this when estimating the required sample size due to the complex assumptions the calculations require, leading to uncertainty of how much reduction in the required sample size can be expected.

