### Allocation, randomization, and masking

In phase 1, participants will be randomized to either interventional arm or control arm with a 1:1 allocation ratio, using a computer-generated (Sealed Envelope Ltd., London, UK) blocked randomization schedule with varying block sizes of two or four, stratified by sex (male, female) and centre with equal allocation to all trial arms. For phase 2, only the participants with COPD will continue the maintenance program in their allocated group.

Group allocation will be performed after participants have been recruited into the trial; baseline assessments have been completed and eligibility confirmed. The allocation sequence will be kept in an opaque, tamper-proof sealed, and stapled envelope that will be concealed until the end of the outcome assessment. By using aluminium foil inside the envelope, it will be impermeable to intense light. A delegated person independent from enrolment, assessments, and training will generate the allocation sequence, enrol participants, and assign participants to interventions.

Outcome assessors and data analysts will be masked to group allocation. Participants will be instructed not to reveal their group allocation to the outcome assessor during interim-, 12-week, and 24-month trial assessments. In case of failure of keeping the outcome assessor masked, a second outcome assessor will be available. Given the nature of the interventions, neither participants nor instructors of the training sessions can be masked during the intervention. Hypotheses of the trial will not be revealed to the participants during their participation.

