#### Statistical methods—outcomes

For primary and secondary outcomes with continuous data, treatment effect will be estimated by mean change-from-baseline (delta-value (Δ)) with 95% confidence intervals and the effect size (ES). The between-group effects will be analysed using analysis of covariance (ANCOVA). In the ANCOVA, baseline values, age, sex, centre, and VO_2_peak will be used as covariates. In phase 1, the primary analyses will be one model for the COPD group and one model for HC. In addition, to investigate any differential effects to the interventions between COPD and HC, a two-way ANCOVA including the Group (COPD/HC) × Intervention (supramaximal HIIT/MICT) interaction will be performed. In phase 2, there will be one model with the three arms (supramaximal HIIT, MICT, and usual care). Additional details will be provided in the SAP.

The assumptions of linearity, normality of residuals, and homogenous variance will be checked using residual plots, normal quantile plots, and histograms. Violations of linearity and normality assumptions will be dealt with by transformations of the dependent variable or non-linear modelling of the independent variables. Outliers will not be removed unless there is a methodological reason for it.

Feasibility of intervention outcomes and number of responders will be described with descriptive statistics and analysed with between group (HIIT/MICT) comparisons in both the COPD (phase 1 and 2) and HC group (phase 1).

In phase 1, hospitalization and exacerbations during the intervention will be presented descriptively. In phase 2, mortality, hospitalizations, and exacerbations will be presented with descriptive statistics and analysed using Kaplan–Meier curves and Cox proportional hazard models.

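### The article names no prior-event covariate for the phase 2 exacerbation and hospitalisation models, although the history is collected and usual care is not randomised

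*Protocol article*

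**What the plan says.** All references are to the protocol article.

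- **Data in hand.** The section *Assessments only at baseline* lists "exacerbations, and hospitalisations during the last 12 months". It introduces the baseline-only items as "measures with the purpose to characterize the participants and are only considered outcomes for cross-sectional comparisons between groups at baseline".
- **Event analysis.** Under *Statistical methods—outcomes*, phase 2 "mortality, hospitalizations, and exacerbations will be presented with descriptive statistics and analysed using Kaplan–Meier curves and Cox proportional hazard models". No covariates are named for the Cox models.
- **Covariates elsewhere.** The section *Multicentre trial and covariates* says "we will adjust the analysis for the predictive covariates age, sex, VO_2_peak, and centre". For continuous outcomes, "In the ANCOVA, baseline values, age, sex, centre, and VO_2_peak will be used as covariates".
- **Allocation.** HIIT versus MICT is randomised, "stratified by sex (male, female) and centre with equal allocation to all trial arms". Usual care is different: "As the usual care arm is not included in the randomization, phase 2 is a partially randomized controlled trial". It is matched to the exercise arms "by age, sex, disease severity (GOLD A/B/E), educational level, and physical activity".
- **Companion analyses and deferral.** The section on analysis population and missing data promises both adjusted and unadjusted analyses. Further statistical detail is left to a separate SAP, which is to be final before database lock and unblinding.

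**The concern.** The article adjusts each continuous outcome for the participant's own baseline value. The equivalent for an event outcome is the participant's own event history. That history is recorded in the year before entry, yet it appears neither in the stated covariate list nor among the matching factors.

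In the two usual-care contrasts no randomisation balances event history. If the usual-care participants had more exacerbations or admissions before entry than the exercise participants, and matching does not remove the difference, a Cox model without that history will credit the difference to training. If they had fewer, it will hide a benefit.

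In the randomised HIIT versus MICT contrast no such confounding arises. Leaving out a strong predictor there only pulls the hazard ratio somewhat towards 1 and costs some power.

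**Working it through.** **1. What the text fixes and what it leaves open**

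| Element | Continuous outcomes | Phase 2 event outcomes |
|---|---|---|
| Model | ANCOVA | Kaplan–Meier, Cox |
| Own baseline value in the model | Yes | Not named |
| Age, sex, centre, VO2peak | Named | Not named for Cox; named for the analysis in general |
| Baseline counterpart collected | Yes | Yes, events in the previous 12 months |

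The baseline-only items are not confined to description. Educational level and physical activity are in the same list, and both are used to match usual care.

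**2. Inputs**

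From the article: 46 per arm, 24 months, up to 30% additional drop-out, two-sided alpha 0.05. It states no event rate, hazard ratio or power for the event outcomes, so there is no figure of its own to reproduce. Event rates, between-person variation, imbalance and treatment effect below are assumptions.

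**3. Usual care versus an exercise arm, no true effect**

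Each person has an underlying rate equal to the mean rate times a gamma variable with mean 1. The usual-care rate is multiplied by an imbalance factor. The prior-year count is Poisson with that rate. Time to first event is exponential and is censored at 2 years. A Cox model is fitted with arm alone, then with arm plus a prior-count term (1,500 replicates per scenario).

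With no between-person variation, the false hazard ratio would simply be 1 divided by the imbalance: 1/1.3 = 0.77 and 1/1.5 = 0.67. Variation between people pulls it towards 1.

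Setting A: mean rate 0.5 to 1.2 per year, gamma variance 0.5 to 1.5, no drop-out, term log(1 + count).

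| Imbalance | HR without | HR with | False positives without | False positives with |
|---|---|---|---|---|
| 1.3 | 0.82–0.87 | 0.85–0.95 | 8–14% | 5–10% |
| 1.5 | 0.71–0.80 | 0.75–0.92 | 13–25% | 7–17% |

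Setting B: mean rate 0.75, variance 0.5 or 1.0, 30% of participants dropping out uniformly over follow-up, term log(count + 0.5).

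| Imbalance | HR without | HR with | False positives without | False positives with |
|---|---|---|---|---|
| 1.25 | 0.84–0.86 | 0.88–0.90 | about 9% | 7–8% |
| 1.5 | 0.72–0.75 | 0.78–0.84 | 17–26% | 10–16% |
| 2.0 | 0.57–0.63 | 0.67–0.76 | 41–59% | 17–33% |

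The term removes part of the bias. One year's count is a noisy measure of a person's rate, so some confounding remains. With balanced arms and no effect, both models reject at about 4 to 6%.

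To see what a coarse class could carry, setting B was also run with only an indicator of two or more prior events. At an imbalance of 1.5 the hazard ratio was 0.76 to 0.81.

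**4. HIIT versus MICT, within-person hazard ratio 0.6**

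Same model with balanced arms and 30% drop-out:

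| Mean rate | Variance | HR without → with | Power without → with | Gain (points) |
|---|---|---|---|---|
| 0.5 | 0.5 | 0.634 → 0.626 | 26.1% → 27.6% | 1.5 |
| 0.5 | 1.0 | 0.661 → 0.640 | 23.5% → 25.5% | 2.0 |
| 1.0 | 0.5 | 0.658 → 0.640 | 33.3% → 36.8% | 3.5 |
| 1.0 | 1.0 | 0.695 → 0.653 | 23.1% → 29.7% | 6.6 |

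The gain grows with the variation between people. As a cross-check on scale, Schoenfeld's formula, power = Φ(|ln HR| × √(D/4) − 1.96), gives for HR 0.6 and D = 28, 46 and 64 events (30%, 50% and 70% of 92) 27%, 41% and 53%. Power is low either way.

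**The case against.** The strongest reply has four parts.

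- **The baseline section restricts nothing relevant.** A reader might infer that it reserves prior events for describing the sample, so that the event models must omit them. The text does not support this. It limits those measures as outcomes, and two of them are used for matching. This objection stands in full.
- **The Cox covariates are unstated, not wrongly stated.** The list of four sits in the sample-size rationale and in the ANCOVA, and the SAP may add to it. So one cannot say that the models will carry no such term. What remains is that the article describes a general adjustment set and an own-baseline rule, and neither reaches the event outcomes although the data are in hand.
- **Matching already addresses some of this.** Usual care is matched on GOLD A/B/E. The article does not define these classes; if class E reflects exacerbation history, matching carries a coarse version of it. The imbalances above are imposed with no matching step, so they describe residual imbalance and do not predict what the planned design will produce. Recent exacerbators, within 6 weeks and with a change in medication, are also excluded. This lowers the likely size but does not bring the history into the model.
- **HIIT versus MICT is randomised.** A reader might take the difference between the hazard ratios with and without the term as bias from allocation. It is not: the two estimate different quantities, one conditional on prior events and one marginal. Only a small gain in efficiency is at issue, and the article claims no power for these outcomes.

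**Conclusion.** The point holds in a limited form. The article names no prior-event covariate for the phase 2 exacerbation and hospitalisation models, and its stated list omits one, although the data are collected.

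The usual-care contrasts are the main concern. If matching leaves a 1.5-fold difference in underlying rate and training has no effect, the apparent hazard ratio is about 0.71 to 0.80 without the term and 0.75 to 0.92 with it. Adjustment reduces the confounding but does not remove it. HIIT versus MICT gains about 1.5 to 6.6 percentage points of power in the four scenarios shown.

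All these figures rest on assumed rates, heterogeneity and imbalance. They concern first exacerbations; no hospitalisation scenario was run. These are secondary outcomes, and the primary analyses are not affected. The change is worth making because it is nearly free.

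**What to change.** In *Statistical methods—outcomes* and in the SAP:

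1. Add log(1 + exacerbations in the previous 12 months) to the exacerbation model, beside age, sex, VO2peak and centre.
2. Add hospitalisations in the previous 12 months, as yes/no or log(1 + n), to the hospitalisation model in the same way. Fix the form in advance.
3. Keep the unadjusted result as the companion analysis already promised.
4. Describe the usual-care event contrasts as observational, with or without adjustment.

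The section *Assessments only at baseline* needs at most a sentence saying that these two variables also serve as covariates.

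The cost is wording and one degree of freedom per model. No new data are needed, and the change can be specified in advance if it is made before the SAP is finalised.

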
### Outcomes

Primary and secondary outcomes are assessed at baseline, 12 weeks and 24 months if not stated otherwise. The analysis metric is change from baseline at 12 weeks (phase 1) and change from baseline at 24 months (phase 2), if not stated otherwise. Outcomes will be aggregated as mean ± SD or median (interquartile range) depending on distribution of data, unless otherwise specified.

Before, during and after all physical tests, the level of dyspnoea and leg fatigue (0–10, arbitrary units) on the [47] CR-10 scale [47] and perceived exertion (6–20, arbitrary units) on the [47] RPE scale [60] will be assessed. An overview of outcome assessments is outlined in Table 5 (SPIRIT Figure).

**Table 5 Tab5:** Time schedule of enrolment, assessments and visits for participants

		Screening	Baseline					Allocation	Phase 1	Interim	Follow-up assessments				Phase 2	Follow-up assessments			
Timepoint		-T6	-T5	-T4	-T3	-T2	-T1	0		T1	T2	T3	T4	T5		T6	T7	T8	T9
Timeline (weeks)			-3 to -1					0	0-12	6	13-14				15-102	103-104			
**ENROLMENT**:																			
Eligibility screening		X																	
Informed consent			X																
Allocation^c^								X											
**INTERVENTIONS**:																			
HIIT/MICT/Usual care									X						X				
**ASSESSMENTS**:																			
**Visit 1 - Baseline only**																			
Physical activity		X																	
mMRC and self-MNA		X^a^	X																
Lung function			X																
Medical history and demographic data			X																
**Visit 1**																			
CPET and BCST			X							X	X					X			
MoCA, CAT and CRQ^d^		X^b^	X								X^f^				X	X			
Quadriceps function tests			X								X					X			
**Visit 2**																			
Body composition				X								X					X		
Cardiovascular function				X								X					X		
Global cognitive function				X								X					X		
Constant work-rate test				X								X					X		
HADS and EQ-5D-5L				X								X					X		
5-time sit-to-stand and stair climb power test				X								X					X		
**Visit 3**																			
Blood sampling					X								X					X	
Blood pressure					X								X					X	
Muscle biopsy^c^					X								X						
**Visit 4**																			
Brain magnetic resonance imaging						X								X				X	
**Visit 5**																			
PET/CT^e^							X												X
I**nterventional**																			
Feasibility^c^									X						X				
Adverse events									X						X				
Exacerbations / hospitalisations / mortality									X						X				

Schedule of enrolment, interventions and assessments. The number of weeks can vary slightly depending on schedueling and thus time needed for follow-up assessments (2-3 weeks) and weeks of rest before starting the phase 2 (1-2 weeks). The schedule is representative for participants in Umeå, Sweden, minor differences exist for participants in Hasselt, Belgium, due to logistics

*HIIT* supramaximal high-intensity interval training, *MICT* moderate intensity continuous training, *mMRC* Medical Research Council Dyspnea Scale, *MoCA* the Montreal Cognitive Assessment test, *CPET* cardiopulmonary exercise test, *BCST* Borg cycle strength test, *CAT *COPD assessment test, *CRQ* Chronic Respiratory Disease Questionnaire, *HADS* Hospital Anxiety and Depression Scale, *MNA* Mini-Nutritional Assessment, *PET/CT* positron emission tomography/computed tomography

^a^only mMRC is used for screening

^b^only CAT is used for screening

^c^not for usual care group

^d^not for HC group

^e^only for those enrolled at Umeå, Sweden

^f^(superscripted) MoCA is only performed at baseline at 24-months

### Primary outcomes

Phase 1 and phase 2 include the same three primary outcomes. These are multiple primary outcomes and not co-primary outcomes. Each outcome is deemed sufficient on its own to establish intervention efficacy. Multiple primary outcomes are selected in the COPD-HIIT project as we intend to determine the effects on multiple extrapulmonary manifestations of the disease which cannot be adequately quantified using a single primary outcome [61–63].

#### Global cognitive function

Global cognitive function will be assessed as the z-score determined by the performance on five tests from the Cambridge Neuropsychological Test Automated Battery (CANTAB) and the trail making test [64] (TMT). To create a global cognitive score, we will convert the six separate test scores from the CANTAB tests and the TMT to a composite z-score (Table 6).

**Table 6 Tab6:** Overview of cognitive test battery structured per cognitive domain

Cognitive test	Description	Outcome measure	Unit
*Domain: Attention and psychomotor speed*			
Motor screening task^a^ (CANTAB)	Colored crosses (“stimuli”) appear in various locations on the screen. The participant must select the cross as quickly and accurately as possible.	**1. Mean latency for a participant to correctly respond to the stimulus on screen during assessed trials**	milliseconds
		2. Total number of correct responses a participant made across all assessed trials	number
		3. Total number of incorrect responses a participant made across all assessed trials	number
Reaction time (CANTAB)	Participants must select a button on the screen. Circles are presented above the button and the participant is asked to react as soon as possible once a yellow dot appears in one of the circles by clicking the corresponding circle. The assessment entails two tasks: - Simple task: one circle above button - Five-choices task: five circles above button.	**1. Mean reaction time in** simple and **five-choices task**	milliseconds
		2. Mean movement time in simple and five-choices task	milliseconds
		3. Total error score in simple and five-choices task	number
		4. Inaccurate response error score in simple and five-choices task	number
		5. No response error score in simple and five-choices task	number
		6. Premature responses error score in simple and five-choices task	number
		7. Inaccurate location error score in five-choices task	number
Rapid visual information processing (CANTAB)	A white box is shown in the center of the screen where digits from 2 to 9 appear in a pseudo-random order at the rate of 100 digits per minute. Participants are requested to detect target sequences of digits (e.g., 2-4-6, 3-5-7, 4-6-8). When the participant sees the target sequence, they must respond by selecting the button in the center of the screen as quickly as possible.	**1. A prime: signal detection of a participant’s sensitivity to the target sequence regardless of response tendency, i.e. measure of how good the participant is at detecting target sequences**	-
		**2. Probability of hit: the number of target sequences during assessment blocks that were correctly responded to within the time allowed, divided by the number of target sequences during assessment blocks**	-
		**3. Probability of false alarm: the number of sequence presentations that were false alarms divided by the number of sequence presentations that were false alarms plus the number of sequence presentations that were correct rejections**	-
		4. Total hits: the total number of target sequences that were correctly responded to within the allowed time during assessment sequence blocks	number
		5. Total misses: the total number of target sequences that were not responded to within the allowed time during assessment sequence blocks	number
		**6. Mean response latency on trials were the participant responded correctly across all trials**	milliseconds
*Domain: Memory*			
Paired associates learning (CANTAB)	Boxes are displayed on the screen and are opened in a randomized order. One or more of them will contain a pattern. The patterns are then displayed in the middle of the screen, one at a time and the participant must select the box in which the pattern was originally located. The entire assessment contains multiple levels with an increasing number of patterns.	1. Errors: the total number of times a participant selected an incorrect box when attempting to recall a pattern location (expressed for the entire assessment and per level)	number
		**2. Adjusted errors: the total number of times a participant selected an incorrect box when attempting to recall a pattern location, plus an adjustment for the estimated number of errors they would have made on any assessment level, attempts and recalls they did not succeed on (expressed for the entire assessment and per level)**	number
		3. Attempts: the total number of attempts made by the participant during assessment levels (expressed for the entire assessment and per level)	number
		4. Mean errors to success: the mean number of attempts needed by a participant to successfully complete the level	number
		**5. First attempt memory score: the number of times a participant chose the correct box on their first attempt when recalling pattern locations**	number
		6. Number of patterns reached: the number of patterns presented to the participant on the last level they reached	number
Spatial working memory (CANTAB)	Several colored boxes are shown on the screen. The aim of this test is that, by selecting the boxes and using a process of elimination, the participant should find one yellow ‘token’ in each of several boxes and use them to fill up an empty column on the right-hand side of the screen. The entire assessment contains multiple levels with an increasing number of boxes.	**1. Between errors: the number of times the participant incorrectly revisits a box in which a token has previously been found (expressed for the entire assessment and per level)**	number
		2. Within errors: the number of times a participant revisits a box already shown to be empty during the same search (expressed for the entire assessment and per level)	number
		3. Double errors: the number of times a participant commits an error that is both a within error and a between error (expressed for the entire assessment and per level)	number
		4. Total errors: the total number of times a box is selected that is certain not to contain a token and therefore should not have been visited by the participant (expressed for the entire assessment and per level)	number
		**5. Strategy: the number of times a participant begins a new search pattern from the same box they started with previously**^b^	number
		6. Level reached: reports the level number that the participant reached but did not necessarily completed	number
Verbal recognition memory (CANTAB)	The participant is shown a list of words to remember. During the recognition phase, the participant is asked to say whether they remember seeing the word on the screen before. The word can be one of the originals, or a new word (distractor) which they have not yet seen before.	1. Free recall distinct stimuli: the total number of distinct words that are correctly recalled from the presentation phase	number
		2. Free recall novel words: the total number of novel words that were given by the participant which were not shown during the presentation phase	number
		3. Free recall perseverations: the number of times a participant repeats a word that was shown during the presentation phase	number
		**4. Immediate total correct: the total number of target words that the participant correctly recognizes plus the total number of distractor words that the participant correctly rejects**	number
		5. Immediate correct to stimuli: the total number of words that the participant correctly recognizes in the immediate recognition phase	number
		6. Immediate correct to distractors: the total number of times the participant correctly responds “no” to a distractor word in the immediate recognition phase	number
		7. Immediate incorrect to distractors: the total number of times the participant incorrectly responds “yes” to a distractor word in the immediate recognition phase	number
		**8. Delayed total correct: the total number of target words that the participant correctly recognizes in the delayed recognition phase, plus the total number of distractor words that the subject correctly rejects**	number
		9. Delayed correct to stimuli: the total number of words that the participant correctly recognizes in the delayed recognition phase	number
		10. Delayed correct to distractors: the total number of times the participant correctly responds “no” to a distractor word in the delayed recognition phase	number
		11. Delayed incorrect to distractors: the total number of times the participant incorrectly responds “yes” to a distractor word in the delayed recognition phase.	number
*Domain: executive function*			
Trail making test	The test consists out of two parts, A and B, and is performed with paper and pencil. During part A, the participant needs to connect 25 digits in ascending order (1 to 25) as fast as possible by drawing lines between the digits. During part B, the participants need to connect 13 digits in ascending order (1 to 13) and 12 letters (A to L) in alphabetical order, alternating digits, and letters (i.e., 1 – A – 2 – B – 3 – C, etc.) as fast as possible by drawing lines between the digits and letters.	**1. Time of completion part A and B**	seconds
		2. Amount of errors part A and B	number
		**3. Time of completion part B/part A**	-
		**4. Time of completion part B minus part A**	seconds

^a^the motor screening task will not be used for the calculation of the global cognitive score. This test is a screening task to make sure there are not sensorimotor deficits or lack of comprehension present

^b^strategy is also a measure of executive function

Cognitive function is selected as a primary outcome as the research on cognitive function and brain health in people with COPD is scarce [27, 28], and the pathogenesis of cognitive dysfunction is not fully understood. A global cognitive score constitutes the primary outcome, as recommended by the outcome of a recent Nature meta-analysis on the effects of exercise on cognition [65]. Current research on exercise prescription and treatment of cognitive dysfunction in people with COPD is still in the initial stages [27, 29, 37]. To our knowledge, no trial has compared the effect of different exercise intensities on global cognitive function in people with COPD.

The CANTAB is quick to set up and easy to administer, measuring sustained attention, psychomotor speed, episodic memory, working memory, and executive function. The cognitive test battery has been used in various populations but not yet in COPD. The separate cognitive domains have, however, previously been assessed in individuals with COPD following exercise training [27, 66]. The CANTAB will be administered in country-specific translations using the CANTAB Connect Research software on an Apple iPad in a quiet room. Automated voiceover and written instructions will be given by the software. The test battery takes around 60 min to complete, and an assessor will be nearby and available for any questions. The TMT is a widely used neuropsychological test tool to evaluate executive functions such as selective attention and cognitive flexibility. The test is administered into two parts, TMT-A and TMT-B (Table 6).

In addition to the global cognitive score, each separate test score will also be assessed as a secondary outcome (Table 6). The seven tests will be performed in the following order: motor screening task (not included in the calculation of the global cognitive score), spatial working memory, verbal recognition memory, TMT, reaction time, paired associates learning, and rapid visual information processing. Multiple outcome measures are available for each test, with outcomes that are recommended by CANTAB and previously used in similar research [67–69] highlighted in bold in Table 6. Which test-specific outcomes that will be included in the global cognitive score determination will be detailed in the statistical analysis plan (SAP).

